##### Programme monitoring

Both training groups will perform the first eight sessions using indoor cycling ergometers, another four lessons using a treadmill and the remainder in outdoor green areas of the city.

Across the sixteen sessions participants will be able to practise and to become familiar with a variety of exercise forms, while keeping to the training goals. The aim is that this experience allows them to feel more empowered with respect to physical activity.

At the beginning of the programme, participants will be given a heart rate monitor (Geonaute, ONRhythm 110, Oxylane, Villeneuve d’Ascq, France) that will be used to monitor the training intensity during supervised and self-administered sessions.

Additionally, a web-based application will be used to monitor and provide feedback for the self-administered training sessions.

#### Educational resources

Educational resources for supporting the counselling programme, such as the participants’ guide [25], have been validated by means of Delphi qualitative techniques [28], patient interview, quantitative questionnaires [29, 30] and the INFELZ software [31].

### Outcome measures

Measurements will be taken before (t0 = 0 months) and after (t1 = 16 weeks) the intervention. As a medium-term follow-up measure, the exercise and control groups will also be assessed 24 weeks later (t2) (Fig. 1). Table 3 shows a detailed outline of the outcome measurements.

**Table 3 Tab3:** BELLUGAT protocol schedule form and procedures for all interventions

Time point	Enrolment	Baseline assessment	Allocation	+16 weeks assessment	+24 weeks assessment
	t-1	t0		t1	t2
*Preliminary data*:					
Eligibility screen	✔				
Informed consent	✔				
Allocation			✔		
*Anthropometric measurements*					
Body mass		✔		✔	✔
Height		✔		✔	✔
Body mass index		✔		✔	✔
Waist circumference		✔		✔	✔
Hip circumference		✔		✔	✔
*Blood sampling and biochemical measurements*					
Lipid profile (TG, TC, HDLc, LDLc)		✔		✔	✔
Plasma glucose		✔		✔	✔
Plasma glycated haemoglobin		✔		✔	✔
Plasma adiponectin		✔		✔	✔
Plasma Interleucin-6		✔		✔	✔
Plasma metabolome-lipidome		✔		✔	✔
Plasma MicroRNA		✔		✔	✔
*Medical procedures*					
Resting blood pressure		✔		✔	✔
Cardiorespiratory fitness (VO_2_peak)		✔		✔	✔
*Physical activity and sedentary behaviour*					
Physical activity (LPA and MVPA)		✔		✔	✔
Sedentary time		✔		✔	✔
*Self-reported Questionnaires*					
Food frequency questionnaire		✔		✔	✔
Healthy eating index		✔		✔	✔
Empowerment related to health		✔		✔	✔
Physical activity and dietary habits self-efficacy		✔		✔	✔
Health related quality of life (EQ-5D)		✔		✔	✔
Direct costs				✔	
Indirect costs				✔	
Demographic variables		✔			
Enjoyment with the programme				✔	
Reasons for abandoning		✔		✔	✔

*EQ-5D* EQ-5D questionnaire, *HDLc* High Density Lipoprotein cholesterol, *LDLc* Low Density Lipoprotein cholesterol, *LPA* Light Physical Activity, *miRNA* microRNA, *MVPA* Moderate-to-Vigorous Physical Activity, *TC* Total Cholesterol, *TG* Triglycerides, *VO*
_*2peak*_ Peak Oxygen uptake

All assessments will be divided into two appointments. In the first appointment, fasting blood samples will be drawn through an antecubital vein, and anthropometric (body mass, height, waist and hip circumferences) and body composition measures (percentage of fat) will be obtained. Also during this appointment, accelerometers will be positioned on the participants’ waist and they will be given instructions on how to complete an activity log during the 7-day period that they will wear the accelerometers.

In the second assessment appointment, participants will be asked to complete the questionnaires on health-related quality of life, self-efficacy, empowerment and dietary habits. Resting (recumbent and sitting) ECG and blood pressure measures will then be taken. Finally, participants will also complete a voluntary maximal graded test on a cycle ergometer.

Accelerometers will be retrieved at the end of the 7-day period during which participants have recorded their free-living movement.

#### Risk factors for metabolic syndrome

##### Anthropometry and visceral adiposity

Body mass (precision: 0.1 kg) and height (precisions (0.1 cm) will be measured with a scale (SECA 711, Hamburg, Germany) and stadiometer (Año-Sayol, Barcelona, Spain), with the participant in underwear and barefoot, following standard procedures [32]. Body mass index (BMI) will be calculated by dividing body mass (kg) by height (m^2^).

Waist circumference (WC) (precision: 0.1 cm) will be measured in triplicate at the end of several consecutive natural breaths, at a level parallel to the floor, at the midpoint between the top of the iliac crest and the lower margin of the last palpable rib in the mid-axillary line. Hip circumference (HC) (0.1 cm) will also be measured in triplicate at a level parallel to the floor, at the largest circumference of the buttocks. Both measures will be made with a stretch‐resistant tape and without constricting [33]. The mean of the three measurements will be used in the waist-to-hip ratio calculation (WtHr).

##### Blood pressure

Blood pressure (BP) will be measured at the level of the brachial artery of the dominant arm using an automated device (Omron M, Omron Healthcare Europe B.V. Hoofddorp, The Netherlands), with participants in a relaxed sitting position. Measurements will be taken in duplicate, 2 min apart. The latter of these will be recorded [34].

##### Plasma biochemistry

Blood samples for the determination of plasma triglycerides (TG), total cholesterol (TC), low-density lipoprotein cholesterol (LDLc), high-density lipoprotein cholesterol (HDLc), glycated haemoglobin (HbA1c) and glucose will be drawn after an overnight fast, with participants in a sitting position. Blood samples will be analysed with automated methods at the laboratory of the Arnau de Vilanova University Hospital (Lleida).

#### Metabolic risk score

A continuous metabolic syndrome risk score (cMSSy) will be calculated, as described by Wijndaele [35]. The score contains the five risk factors considered in the definition of metabolic syndrome [1, 36], namely waist circumference, TG, HDLc, systolic blood pressure (SBP) and plasma glucose.

#### Systemic inflammation and adipose tissue parameters

Fasting blood samples will also be used to determine inflammation parameters (adiponectin and interleukin (IL)-6). Inflammation parameters will be measured by immune assay using high sensitivity *MILLIPLEX®XMap* commercial kits *(*Millipore, Billerica, MA, USA). The visceral adipose tissue index will be calculated following the procedure described by Amato [37]; which relates waist circumference, body mass index, triglycerides and HDLc.

#### Plasma microRNA determination

We will analyse miR-197, miR-23a, miR-509-5p, miR-130a-b, miR-195, miR-27a and miR-320, which are known to be deregulated and associated with features of metabolic syndrome. Targeted microRNA will be determined after its extraction from blood samples, following the instructions provided with the MagMax mirVana RNA isolation kit. In addition, any microRNA will be quantified by a specific TaqMan Advanced miRNA assay.

#### Untargeted and targeted metabolomics and lipidomics

Metabolomics and lipidomics will be performed after the extraction of metabolites and lipids from plasma/serum at the baseline and final stages of the experiments. Metabolites and lipids will be separated by UPLC and detected by QTOF and TQP, depending on the procedure. Species identification will be performed via the PCDL database of Agilent Technologies, which uses retention times in a standardized chromatographic system as an orthogonal searchable parameter to complement accurate mass data (accurate mass retention time approach). In both cases, the SMPDB database [38, 39] will be used for querying metabolites obtained from the HMDB search, using a 0.05 Da M.W. tolerance and the Metaboanalyst platform [40, 41] for the determination of differential features.

#### Cardiorespiratory fitness

Cardiorespiratory fitness will be assessed by means of voluntary maximal graded exercise on a cycle ergometer (Monark 828E, Monark, Sweden).

Before the exercise test, measures will be taken of heart rate and systolic (SBP) and diastolic (DBP) blood pressure, along with a resting electrocardiogram (ECG). Electrocardiographic leads will be positioned according to Mason-Likar placement [42].

These tests will be performed at a constant cadence of 60 rpm. The warm-up stage will be 2 min at 10 W (W). The stepwise graded exercise will then begin, with increases of 20 W every two minutes until volitional fatigue or until participants cannot maintain the pre-established cadence. The recovery stage will be 3 min at the load selected by the participant.

During the graded exercise, oxygen uptake and ventilation will be measured using the Oxycon Mobile metabolic system (Oxycon Mobile, Carefusion, Germany). Gas calibrations will be conducted before each test. Heart rate will be measured using a Polar 610 s chest heart rate monitor (Polar Electro YO, Kempele, Finland) and an electrocardiographic device (Kaunas Load System, Kaunas, Lithuania).

SBP and DBP will be measured using a manual device (Omrom M, Omron Healthcare Europe B.V. Hoofddorp, The Netherlands) at rest, every 2 min during the final 30 s of each stage and at 2, 4 and 6 min of the recovery.

Ratings of perceived exertion (RPE) will be obtained every 2 min using the 10-point Borg scale [43].

Capillary blood samples (200 μL) from the ear lobe will be taken at baseline and at the sixth minute of the post-exercise period for the analysis of plasma changes due to exertion (miRNA determination and untargeted and targeted metabolomics and lipidomics).

Data from the exercise test will be recorded for the screening of abnormal BP and ECG responses, eliciting either VO_2max_ or VO_2peak_, as well as for determining subsequent exercise prescriptions. The criteria for achieving VO_2max_ will be RER >1.1, a plateau in VO_2_ (change of <100 mL · min^−1^ in the final two consecutive stages), and a HR within 10 beats · min^−1^ of the maximal level predicted by age [7]. Those participants who do not meet these criteria will be classified as having reached their VO_2peak_.

The cycle ergometer test is preferred here to the treadmill test because it is easier to take the ECG and BP measurements, and because during the intervention most of the training sessions will be group indoor cycling, and hence the transfer of prescribed heart rate will be more valid. In addition, cycle ergometry is safer than treadmill testing.

#### Physical activity habits and sedentary behaviour

Active and sedentary habits will be assessed objectively by accelerometry using the ActiGraph GT3X+ accelerometer (ActiGraph LLC, Pensacola, FL, USA) over eight consecutive days. Accelerometers will be positioned laterally on each participant’s waist and attached with an elastic belt. Participants will be instructed to wear the accelerometer all day, including during sleep. Accelerometers will be programmed to register the movement in 60-s epochs and data will be downloaded and analysed with ActiLife 6.0 software (ActiGraph, Pensacola, FL, USA). Sleeping hours and 20-min bouts of consecutive zero counts will be excluded from the analysis. Data from accelerometers will be analysed to yield an overall physical activity index (expressed as vector magnitude in mean counts per minute (CPM)) and the percentage of registered time spent in different levels of sedentary behaviour or physical activity (PA). The cut-off points for the categorization of movement intensity will be defined as follows: sedentary behaviour (SB) (<100 CPM); light physical activity (LPA) (100 to 2019 CPM) and moderate-to-vigorous physical activity (MVPA) (>2020 CPM) [44]. Sedentary behaviour will be assessed as the total time engaged in sedentary behaviour and as the daily number and length of sedentary periods. The assessment of physical activity and sedentary behaviour will be complemented with a log of the activities performed during the days on which participants wear the accelerometers.

#### Dietary habits

Data regarding participants’ dietary habits will be obtained using the adult version of the food frequency questionnaire (FFC) [45]. This questionnaire consists of a list of food groups, with participants being required to indicate their intake frequency (daily, weekly or monthly) for each component on the list. This questionnaire has been used previously in longitudinal dietary studies and in studies relating dietary patterns and biological parameters in adults [46].

The *Healthy Eating Index* [47, 48] will be calculated to assess and monitor participants’ dietary status. The Healthy Eating Index (HEI) comprises 10 items, each representing different features of a healthy diet: items 1 to 5 measure the degree of agreement with national dietary guidelines for grains, vegetables, fruit, milk and meat. Items 6 and 7 measure the percentage of total fat and saturated fat in the total energy intake, items 8 and 9 measure cholesterol and sodium intake, and item 10 examines the variety of the respondent’s diet.

#### Empowerment and self-efficacy

Empowerment related to health will be measured with the Spanish version of the Health Empowerment Scale (HES) [49]. This instrument contains 8 items (self-control, self-efficacy, problem solving, psychological coping, stress management, support motivation and decision-making) that are scored on a 5-point Likert scale rating from 5 (strongly agree) to 1 (strongly disagree). Higher scores indicate greater levels of health-related empowerment. The Spanish version of the HES achieved a Cronbach’s alpha (internal consistency) of 0.89, and its content validity is supported by scale and item content validity indexes of 0.98 and 1.0, respectively.

Self-efficacy in relation to physical exercise and dietary habits will be measured with a questionnaire created ad hoc in accordance with the guidelines of Bandura [50]. This instrument comprises 17 items related to physical exercise and 10 items related to dietary habits. Each item is scored on a 100-point scale ranging, in 10-unit intervals, from 0 (cannot do it at all) to 100 (highly certain I can do it). Higher scores indicate greater levels of self-efficacy in relation to exercise and dietary habits.

#### Health-related quality of life

Health-related quality of life (HRQoL) will be determined with the Spanish version of the EuroQoL group EQ-5D questionnaire for adults [51]. The EQ-5D comprises questions related to five dimensions: mobility, self-care, usual activities, pain/discomfort and anxiety/depression. Each dimension has five levels ranging from “no problems” to “extremely important problems”. The EQ-5D also includes a vertical visual analogue scale (EQ VAS) on which respondents self-rate their current perception of health between the endpoints: ‘100 = Best imaginable health state’ and ‘0 = Worst imaginable health state’. The EQ-5D has shown reliability of 0.86 to 0.90.

#### Cost analysis

Direct and indirect costs of setting up and running the interventions will be calculated in order to assess the economic aspect. HRQoL scores will be used to weight survival years and, thus, to generate QALYs (Quality Adjusted Life Years). The cost-effectiveness analysis will be conducted in accordance with the current practice methods for economic assessment [52]. The primary cost-effectiveness outcome will be a reduction in the metabolic risk score.

#### Other measures

##### Demographic and other variables

Variables such as demographic characteristics, personal and family medical history, and medication use will also be registered.

##### Questionnaires used during the intervention phase

During the intervention phase several questionnaires will be used to assess the degree of enjoyment with [53] or the reasons for abandoning the exercise programme.

### Data analysis

#### Timeline of data measurements

Measurements will be taken before (Baseline, t0 = 0 months) and after (t1 = 16 weeks) the intervention. As a medium-term follow-up measure, the two intervention groups and the control group will also be assessed 24 weeks after the end of the programme (t2).

#### Data management

Confidentiality will be ensured by coding participants’ personal data, to which only the researchers and health care professionals will have access.

After randomization, participants will receive an randomization code (unique for each participant and blinded for the statistician). All data will be analysed according to this randomization code. The key to the source data will only be known by the researchers and the research coordinator. The researchers will be familiar with the study procedure, be trained prior to the study and will collect all data for this study.

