#### Blinding

Due to the nature of the intervention, blinding of participants will not be possible as each of them will be aware of the kind of physical exercise they are engaged in. However, during data analysis researchers will be blinded to the intervention allocated to each participant.

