### Risk and burdens

The main expected difficulties are a low adherence rate and the impossibility of blinding the intervention to participants and researchers. However, we will seek to minimize the former by individualizing attention (providing and discussing written feedback reports) during the implementation phase and the latter by blinding researchers to the group to which individuals were allocated.

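### The plan says researchers are blinded to group, but nothing in it keeps those who measure waist and VO2peak at t1 and t2 unaware of the arm

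*Protocol article*

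**What the plan says.** Three sections of the protocol article bear on who is blinded.

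- **Blinding** (under Participants): participants cannot be blinded, but "during data analysis researchers will be blinded to the intervention allocated to each participant". No blinding is promised for data collection.
- **Data management** (under Data analysis): each participant receives a code after randomization, described as "unique for each participant and blinded for the statistician". The section goes on: "The key to the source data will only be known by the researchers and the research coordinator". The researchers will also "be trained prior to the study and will collect all data for this study".
- **Risk and burdens**: one of the main expected difficulties is "the impossibility of blinding the intervention to participants and researchers". The next sentence says the plan will minimize "the latter by blinding researchers to the group to which individuals were allocated", with no restriction to the analysis stage.

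Two outcome descriptions matter here. Under Anthropometry and visceral adiposity, waist circumference is taken by tape and "will be measured in triplicate at the end of several consecutive natural breaths". Under Cardiorespiratory fitness, the graded cycle test runs "until volitional fatigue or until participants cannot maintain the pre-established cadence". Neither section says that the person measuring is unaware of the arm.

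**The concern.** Risk and burdens offers researcher blinding as the remedy for a difficulty that it has just described as the impossibility of researcher blinding. The rest of the article does not supply that remedy where it would be needed, which is when outcomes are measured. Masking the statistician cannot remove a bias that is already in the recorded values.

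The participants know their arm, so the assessor is the main remaining point at which detection bias can be limited. The hypothesis is directional, favouring vigorous exercise. Waist circumference is read by hand, is the only variable in the sample size statement, and enters both the continuous metabolic risk score and the visceral adipose tissue index. A reader who relies on the Risk and burdens sentence would credit the trial with a protection that its procedures do not provide.

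**Working it through.** **Step 1. The statements side by side.**

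| Section | Who is blinded | When |
|---|---|---|
| Blinding | Researchers | Data analysis only |
| Data management | The statistician (through the code) | Not stated |
| Risk and burdens, first sentence | Blinding of researchers called impossible | Not stated |
| Risk and burdens, second sentence | Researchers | No limit stated |

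The Blinding and Data management sections can describe one scheme: open data collection with masked analysis. The conflict lies inside Risk and burdens, and between its unrestricted promise and the other two sections.

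**Step 2. What the key is.** The article speaks of a key to the source data, not of an allocation key. The sentence follows one about a code issued after randomization and hidden from the statistician, so a link to allocation is the likelier meaning. It could instead be a file linking codes to identities. In that case Data management would not by itself show that data collectors know the arm, but still no section would say that they do not.

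**Step 3. Which outcomes are exposed.** Table 3 places the baseline assessment before allocation, so t0 is not exposed; t1 and t2 are. Any arm-related measurement difference at t1 or t2 therefore goes straight into the change from baseline.

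- Waist circumference: hand-read, with palpated landmarks. Triplicate reading reduces random error, not a systematic tendency.
- VO2peak: measured by gas analyser under fixed cadence and load steps, but the end-point is voluntary, so exposure is less direct.
- Triglycerides, HDLc and glucose: automated laboratory methods, little exposed.
- Resting blood pressure: automated device, little exposed.

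**Step 4. Scale, for illustration only.** The plan gives no figure to reproduce here.

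Inputs from the Sample size section: SD 5.3 cm, two-sided alpha 0.05, 35 per group, 20% drop-out, so 35 × 0.8 = 28 evaluable per arm. Assumed input, not in the documents: a between-arm measurement bias b of 0.5 to 1.5 cm with no true effect.

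Standard error of the difference: 5.3 × √(2/28) = 1.416 cm. The test statistic is shifted by b/1.416. The false-positive rate is the probability that the shifted statistic falls outside its critical values (t with 54 degrees of freedom, ±2.005; normal, ±1.960).

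| b (cm) | b as share of 6.0 cm | Shift b/SE | t-test | Normal approximation |
|---|---|---|---|---|
| 0 | 0% | 0 | 5.0% | 5.0% |
| 0.5 | 8% | 0.35 | 6.4% | 6.4% |
| 1.0 | 17% | 0.71 | 10.7% | 10.9% |
| 1.5 | 25% | 1.06 | 18.0% | 18.5% |

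Sensitivity to n: the intention-to-treat rule with LOCF would analyse up to 35 per arm. If all 35 values carried the bias, the standard error would be 5.3 × √(2/35) = 1.267 cm, and a 1.0 cm bias would give 12.2% (t-test). A baseline value carried forward was taken before allocation and is not exposed, so this is the upper end for a 1.0 cm bias.

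**The case against.** The best defence is that the dedicated Blinding section sets the scheme, Data management fits it, and the sentence in Risk and burdens is loose shorthand: full blinding is impossible, so the problem is reduced by masking the analysis. The word researchers may also mean different people in different sections. On this view only one sentence needs rewording.

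Much of this stands. A reader might infer that the Blinding and Data management sections contradict each other; they do not. A reader might infer that the assessors hold the allocation list; the text makes that probable but does not say it. A reader might also infer that VO2peak will be moved by encouragement from the tester; the article mentions no encouragement.

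The waist procedure is also standardized (landmark, phase of breathing, tape, triplicate), which limits an observer's discretion without removing it. Of the five metabolic risk factors, only waist is hand-read, and cardiorespiratory fitness is a secondary aim. The bias sizes are assumptions, and the pairwise t-test is a simplification, since the plan names repeated measures techniques for the outcomes.

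The defence does not explain how masking at analysis reduces the consequences of unmasked measurement. Nor can it be left to a fuller document, because the article itself makes statements that do not fit together.

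**Conclusion.** The point holds in limited form. The mitigation claimed in Risk and burdens is not delivered for the assessor-dependent outcomes, because no section keeps the t1 and t2 measurers unaware of the arm. This matters mainly for waist circumference and less directly for VO2peak; laboratory outcomes and resting blood pressure are little affected.

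If a 1.0 cm between-arm bias occurred, the false-positive rate for one pairwise comparison would be about 11% instead of 5% (about 6% at 0.5 cm, about 18% at 1.5 cm). This rests on 28 per arm, SD 5.3 cm, no true effect and an assumed bias. It shows how sensitive the trial would be and is no evidence that such a bias will arise. The documents do not support the stronger conclusion that the waist results will be biased towards the interval-training arm; they show only that the plan leaves this open.

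**What to change.** 1. **Data management:** keep any file that links codes to allocation with the IDIAP, which already generates the sequence, and the research coordinator. Remove the researchers from the sentence on who knows the key.
2. **Blinding:** state that the existing staff who measure waist and run the exercise test at t1 and t2 are not told the arm and, where current staffing allows, do not deliver counselling or training. The article assigns counselling to a nurse and training to exercise experts, so this looks feasible, but it does not say that those people never measure; the sponsor should confirm it. Ask participants not to reveal their arm.
3. **Risk and burdens:** reword to match items 1 and 2, so that the three sections agree on who is blinded and when.
4. **If this cannot be done with existing staff:** delete the mitigation claim from Risk and burdens and state that outcome assessment is unblinded.

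The cost is custody of one file and changes of wording. Some participants will still reveal their arm, so blinding will be incomplete; such cases can be logged.
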